### **Specific Aims**

This multicenter study will enroll 100 patients with acute traumatic cervical and thoracic SCI who have a lumbar intrathecal catheter inserted within 48 hours of their injury. The lumbar intrathecal catheter will be inserted pre-operatively for the measurement of ITP and the collection of cerebrospinal fluid (CSF) samples. SCPP will be calculated as the difference between MAP and the ITP.

There are two important distinct yet related objectives in this prospective interventional study.

1. Determine the effect of SCPP maintenance  $\geq 65$  mmHg in acute SCI on neurologic recovery as measured by ASIA Impairment Scale (AIS) grade conversion and motor score improvement.
2. Collect CSF and blood samples for the measurement of neurochemical biomarkers and storage for future biomarker discovery and validation studies.

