We subsequently reported that these proteins were also different between those who experienced AIS grade conversion and those who did not ([Figure 10](#)), and could also be used in combination to predict neurologic outcome [16]. In fact, using Linear Discriminant Analysis modeling, we showed that these 6 biomarkers could predict AIS grade conversion in cervical SCI patients with an accuracy of 86.7% (92.9% accuracy at predicting who would NOT convert) [16]. We also showed recently that in cervical SCI, these CSF biomarkers were far better at classifying injury severity and predicting outcome than MRI measures of the injured cord [20]. In fact, when combining CSF biomarkers, MRI biomarkers, and baseline AIS grade in a logistic regression model to predict neurologic recovery, MRI biomarkers and even the knowledge of the patients' baseline AIS grade did not add anything to the model – *the CSF biomarkers were the only significant variables for predicting outcome*.

**Figure 10.** CSF biomarkers are significantly higher in those who do not convert their AIS grade (NO) as compared to those who do (YES). The y-axis is a log 10 scale, so that a 1-point difference is a 10x difference in concentration. Modified from Kwon et al. J Neurotrauma, 2017.

[figure not shown]

Because we will insert lumbar intrathecal catheters to manage SSCP in this proposal, we can collect CSF samples for the measurement of these 6 CSF biomarkers. **Hence, in this proposal, we will utilize these CSF biomarkers to additionally control for the severity of neurologic impairment and predict recovery.** This will help us in interpreting the true effect of SSCP management on neurologic recovery. For example, if CSF biomarkers from the AIS A patients indicate that they have a 92.9% likelihood of remaining AIS A, and yet AIS grade improvement does occur with SSCP management, then the biomarkers can help us to distinguish this recovery from the variability of spontaneous recovery. It should be noted that while these 6 CSF proteins (IL-6, IL-8, MCP-1, tau, GFAP, and S100β) represent just a handful of the many potential biomarker candidates, they are the proteins that we have studied most extensively and therefore understand the best.

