## 4. ELIGIBILITY CRITERIA

### 4.1. Inclusion Criteria

Patients who meet the following inclusion criteria are eligible for admission into the study:

- Lumbar intrathecal catheter to be inserted as part of clinical hemodynamic management and CSF sample collected **within 48 hours of injury**
- Initial blood sample collected **within 24 hours of injury**
- Male or Female  $\geq 17$  (or the provincial age of majority – depending on local REB guidelines)
- Complete (AIS A) or incomplete (AIS B, C) acute traumatic spinal cord injury
- Bony spinal levels between C0 and T12 inclusive
- Blunt (non-penetrating) spinal cord injury treated either surgically or non-surgically
- Able to communicate in English, or with a translator where available, and provide informed consent

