### 8.2. CSF Biomarkers for Injury Stratification and Prediction of Outcome

Based on past work, the CASPER trial will utilize CSF biomarkers to help in the stratification and prediction of outcome. The CSF will be obtained at ~24 hours post-injury from the intrathecal catheter that is installed as part of the hemodynamic management of the patient.

The CSF biomarkers that will be specifically targeted include: IL-6, IL-8, MCP-1, GFAP, S100 $\beta$ , and tau. CSF will be analyzed using a Meso Scale (Meso Scale Discovery, Rockville, MD) multiplex electrochemiluminescent antibody detection assay for IL-6, IL-8, TNF-R1, MCP-1, and IP-10, using a custom 5-plex kit (K15067M, F210V). Plates will be read on the QuickPlex SQ 120 (Meso Scale Discovery), and the data will be analyzed using MSD Discovery Workbench software.

CSF levels of total tau (T-TAU; KHB0042, Invitrogen), S100 $\beta$  (RD192090100R; Biovendor, Modrice, Czech Republic) and GFAP (RD192072200R; Biovendor) will be determined using specific commercially available enzyme-linked immunosorbent assay (ELISA) kits. For each of these individual ELISAs, the assay sensitivities for tau, S100 $\beta$ , and GFAP are 10pg/mL, 15pg/mL, and 45pg/mL, respectively. The intra-assay coefficients of variation (CV) have been less than 5.9, 3.8, and 6.4%, and inter-assay CVs have been less than 9.0, 10.1, and 6.1 for tau, S100 $\beta$ , and GFAP respectively. Concentration levels of these structural proteins were determined based on a standard curve generated on each plate using manufacturer-supplied reagents. For each analyte,

samples have been assayed in duplicate and average concentrations were used for statistical analysis.

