**Analysis Plan.** We will use multivariable linear and logistic regression to model the association between the intervention (SCPP management vs. MAP management) and neurologic outcome (motor score improvement or rate of AIS grade improvement). Anticipated co-variables to control for include AIS grade, neurologic level, baseline motor score, 24 hr post-injury CSF biomarker levels, age, and gender. As a sensitivity analysis we will utilize propensity score matching, a statistical approach that we have employed previously in an assessment of methylprednisolone for acute SCI [41].

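### The AIS-improvement logistic model may carry about 13 slopes on an assumed 48–76 events; a Firth-penalised fit would remove a modest overstatement of the treatment odds ratio

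*Protocol*

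**What the plan says.** Section 10, Analysis Plan, of the Protocol: "We will use multivariable linear and logistic regression to model the association between the intervention". The outcomes are motor score improvement (linear model) and AIS grade improvement (logistic model). On covariates: "Anticipated co-variables to control for include AIS grade, neurologic level, baseline motor score, 24 hr post-injury CSF biomarker levels, age, and gender". Propensity score matching is added as a sensitivity analysis.

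The biomarker count comes from elsewhere. Section 2.5 says "we can collect CSF samples for the measurement of these 6 CSF biomarkers", and Section 8.2 begins the list: "The CSF biomarkers that will be specifically targeted include: IL-6, IL-8, MCP-1, GFAP", followed by S100β and tau. Section 2.5 puts much weight on these markers. It reports that in an earlier logistic model "the CSF biomarkers were the only significant variables for predicting outcome", and also that the markers "could also be used in combination to predict neurologic outcome", there by linear discriminant analysis.

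The AIS categories at entry are three: "Complete (AIS A) or incomplete (AIS B, C) acute traumatic spinal cord injury". The treated sample is fixed in Specific Aims: "This multicenter study will enroll 100 patients with acute traumatic cervical and thoracic SCI". The controls are the 91 CAMPER patients of Section 2.4. Section 10 makes change in total motor score at 6 months the primary outcome. AIS conversion is named in the first aim, and the choice of n=100 is argued from it.

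**The concern.** A logistic model estimated by ordinary maximum likelihood gives log odds ratios that are too far from zero when there are few events per estimated slope. The listed covariates, read naturally, are many for the number of AIS improvements that 191 patients are likely to give.

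The direction matters in this trial. A true benefit of SCPP management would look larger than it is. The comparison is with historical controls, so covariate adjustment is the main protection against confounding, and cutting the covariate list is not an attractive way out. The affected model is not the primary analysis, but it answers half of the first aim and concerns the outcome on which the sample size was argued.

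**Working it through.** **Plan's own figure.** The Protocol states no event count and no events-per-variable figure. A conversion rate cannot be recovered from its n=143 and n=72, because no baseline rate, alpha or sidedness accompanies them. The rate below is therefore an assumption.

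**Slopes.** Treatment 1 + AIS grade (A, B, C) 2 + neurologic level at least 1 + baseline motor score 1 + biomarkers 6 + age 1 + gender 1 = 13.

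**Patients.** 100 + 91 = 191, assuming that all have a 6-month outcome and a 24-hour CSF value.

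**Events and events per slope.** Events = 191 × rate; ratio = events / 13.

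| Rate | Source | Events | Per slope |
|---|---|---|---|
| 25% | assumed | 47.8 | 3.7 |
| 37.0% | Section 2.5, cervical AIS A, another study | 70.7 | 5.4 |
| 40% | assumed | 76.4 | 5.9 |
| 43.2% | Section 2.5, cervical AIS A, another study | 82.5 | 6.3 |

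Catheter insertion and first CSF are allowed up to 48 hours after injury, so some 24-hour values may be absent. An assumed 20% complete-case loss leaves 38–61 events, or 2.9–4.7 per slope.

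**Primary model for comparison.** The linear motor-score model has 191 / 13 = 14.7 patients per slope, and this small-sample bias of logistic regression does not arise there.

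**Simulation.** There were 12 settings of 1,500 runs each: 91 controls and 100 treated, event rate 25% or 40%, pairwise biomarker correlation 0.3, 0.6 or 0.8, outcome driven by the mean marker level or by individual markers, mild confounding, true odds ratio 1.6 (log 0.470). All inputs except the cohort sizes and case mix are assumptions. In the table, the score is the mean of the six markers, which leaves 13 − 5 = 8 slopes. The last column is the empirical variance of 13-slope maximum likelihood divided by that of the row.

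| Fit | Bias of log OR | 95% coverage | Variance ratio |
|---|---|---|---|
| Maximum likelihood, 13 slopes | +7% to +16% | 93–95% | 1 |
| Firth, 13 slopes | −3% to +4% | 95–96% | 1.21–1.28 |
| Maximum likelihood, one score, 8 slopes | −3% to +11% | 93–95% | 1.10–1.25 |
| Firth, one score, 8 slopes | −8% to +3% | 95–97% | 1.25–1.40 |

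A ratio of 1.21–1.28 is a variance reduction of 1 − 1/1.21 = 17% to 1 − 1/1.28 = 22%.

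The mean log OR under 13-slope maximum likelihood ran from 0.502 to 0.547, so an odds ratio of 1.6 appears as about 1.65–1.73. The excess of 0.032–0.077 is about 8–16% of the empirical standard error in those settings (0.032/0.397 and 0.077/0.469), which is why coverage suffers little. The Monte Carlo error of each bias figure is 2.1–2.7 percentage points (for example 0.462/√1500 = 0.012, and 0.012/0.470 = 2.5%).

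**Cause.** Averaged over settings, the maximum-likelihood bias is 13.1% at a 25% event rate and 10.0% at 40%. By biomarker correlation it is 11.9% at 0.3, 12.3% at 0.6 and 10.4% at 0.8. It falls as events rise and shows no steady increase with correlation.

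**Second set of runs.** With a true odds ratio of 2.0 and the same assumed event rates, the bias was 9–15% under maximum likelihood, with 92–96% coverage, and within about 3% under Firth with all terms kept. Variance was about 17–21% lower.

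**The case against.** The strongest objection is that the Protocol does not commit to 13 slopes. The covariates are only anticipated, no section says that the biomarker levels enter one by one, and Section 2.5 describes them used in combination. Coding is commonly settled in a statistical analysis plan, which is not at hand, so leaving it open is no defect. This stands, and the point is therefore conditional: it concerns a named method applied to a named list on its natural reading. If fewer terms are used the bias is smaller, though ordinary maximum likelihood with one score still reached +11% in one setting.

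It also stands that the event rate is assumed, that the primary analysis is untouched, and that the harm is moderate. Propensity score matching gives a second view of the effect but does not correct the regression estimate.

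Three stronger readings are tempting and are not supported:

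- A reader might blame collinearity among six markers of severity. Bias did not rise steadily with correlation, and Firth on all 13 terms removes it without merging any markers.
- A reader might conclude that the six markers must be replaced by one score. That is a trade-off: with Firth, the score under-estimated the log OR by up to 8% when individual, weakly correlated markers drove the outcome. In a historical-control design the marker-specific information is part of the confounder control.
- A reader might expect a much larger bias in cervical patients alone. The Protocol plans no cervical-only AIS model; its cervical figure in Section 10 sizes the motor-score comparison.

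**Conclusion.** The point holds in a limited form. If the six markers enter separately, the AIS-improvement model has about 3.7–5.9 events per slope, and ordinary maximum likelihood overstates a true treatment log odds ratio by roughly 7–16%. Intervals still cover close to 95%, so this is an inflated and less precise estimate rather than a false conclusion.

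The size rests on an assumed 25–40% improvement rate, on complete 24-hour CSF data, and on the simulated strength of the covariates. More missing samples would make it worse; a higher conversion rate or fewer terms would make it milder. It is worth changing because the analysis serves the first aim, the error favours the intervention when there is a true benefit, and the remedy is cheap.

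**What to change.** Add to Section 10, Analysis Plan (or to the statistical analysis plan if it governs the detail), before CASPER outcomes are seen: *The model for AIS grade improvement will be fitted by Firth-penalised logistic regression with the listed covariates, including the six CSF biomarkers named in Section 8.2. The treatment odds ratio will be reported with a profile penalised-likelihood 95% confidence interval.* The linear motor-score model needs no change.

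Optionally, add a sensitivity analysis in which one biomarker score replaces the six levels. Build it without reference to outcome and fix its loadings before CASPER outcomes are seen. A predictor trained on CAMPER outcomes should not be used, since it would be over-fitted in the control group only.

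The cost is wording: no patients, samples or visits. The one statistical downside is that Wald tests after a Firth fit are slightly conservative, which is the reason for preferring profile intervals.

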### **Study Design Considerations.**

One question worth addressing is ***“why not just do a PRCT of active SCPP management versus MAP augmentation?”*** There are two practical issues to consider. Firstly, conducting a PRCT in acute SCI is a massive undertaking. Only four pivotal acute SCI PRCTs have ever been successfully completed; the last one (Sygen) finishing almost 20 years ago [42-45]. Our current experience indicates that it has not gotten much easier. Consider that enrolment in the Phase 3 PRCT for Riluzole in acute cervical SCI led by [name] began in 2013, and despite having over

participating 20 sites, enrolment will likely not finish until 2021. The Phase 2 PRCT of minocycline for SCI took over 4 years to recruit 51 patients [46]. Additional Phase 2 acute SCI trials of a MgCl formulation and a  $\beta$ FGF analogue were terminated due to poor enrolment. So, while a PRCT design has obvious advantages, these practical realities must be carefully considered before embarking upon a PRCT in acute SCI.

Secondly, if we were to conduct a PRCT, the “treatment arm” would have intrathecal catheters inserted and active SCPP management to keep SCPP  $\geq$  65 mmHg, while the “control arm” would have intrathecal catheters inserted and routine MAP augmentation. **However, this “control arm” is exactly what our CAMPER study cohort consists of** – patients who had an intrathecal catheter placed but then routine hemodynamic management based on MAP. Given that we possess this prospectively collected CAMPER cohort with well-documented neurologic and hemodynamic data, there is a practical rationale to incorporate this cohort into our proposed study, utilizing contemporary statistical methods to control for confounding variables. One of the confounding variables that we will uniquely be able to control for is the levels of the CSF biomarkers that we have also already collected in our CAMPER patients.

